#### Smart Physiotherapy Activity Recognition System-Home Physiotherapy Technique Adherence

A second supervised learning algorithm will be trained, validated, and optimized to classify the exercise technique from the labeled inertial sensor data collected during the supervised physiotherapy sessions. We anticipate that a CRNN architecture similar to the exercise type classifier will likely be suitable. The validated technique classifier will be used to evaluate the technique adherence from the inertial data collected during unsupervised home sessions.

Anticipated challenges with the proposed supervised learning approach to technique evaluation include class imbalance and recovery-related changes in exercise performance. It is anticipated that many more correct technique training examples may be available for some exercises and that an exercise may be performed incorrectly in ways not observed during the supervised sessions, leading to class imbalance. It is also anticipated that through recovery, the expectation for technique and performance of an exercise may change over time, creating a moving target for the technique classifier. The challenge of class imbalance may be mitigated using several potential approaches including (1) random over and undersampling [117]; (2) cost-sensitive learning [117]; (3) semisupervised learning [118]; (4) anomaly detection [119,120]; and (5) synthetic data augmentation [121]. The challenge of recovery-related performance changes may be mitigated by providing our technique classifier metadata related to the classification task (eg, treatment week, pathology, and surgery) [116], implementing patient-specific ML models using transfer learning, and periodically retraining the ML models through recovery.

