#### Aim 1: Develop and Validate the Smart Physiotherapy Activity Recognition System For Evaluating Shoulder Physiotherapy Adherence

##### Objectives

The related objectives are as follows:

Inertial sensor data are collected during supervised physiotherapy for 120 patients with rotator cuff pathology over full treatment duration (up to 5 months).Technical failures preventing supervised data collection are less than 5%.The SPARS artificial intelligence is trained to classify physiotherapy exercise type and technique with classification accuracy exceeding 90% and 80%, respectively.

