#### Inertial Data Labeling

The researchers will attend a supervised physiotherapy session for each patient once every 2 weeks to record exercise type and technique labels synchronously with inertial data collection, based on the input from the treating physiotherapist. The technique will be labeled as a binary variable, indicating if the treating physiotherapist was satisfied that the exercise was performed correctly (as intended). The treating physiotherapist will also make a record of prescribed home exercises and exercise type and technique evaluations at each supervised physiotherapy session.

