#### Construct Validity

The construct validity of the SPARS adherence measures will be evaluated using cross-validated exercise type and technique classification performance metrics (accuracy, precision, recall, and f1-score) from the labeled inertial data. The cross-validated metrics will be assessed for 3 different fold splitting strategies: (1) by-subject; (2) by-session; and (3) within-session. Respectively, these estimate SPARS performance for (1) new subjects (with no training data); (2) new sessions for subjects with prior training data; and (3) new exercise repetitions within a session from which training data were acquired. The by-session cross-validation most closely approximates the use case in the proposed study and will benchmark SPARS performance against our stated measurable objectives.

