Despite the efforts we have invested in developing a simple, accurate, and robust method for tracking shoulder physiotherapy, tracking errors will inevitably occur and result in imperfect adherence measurement. These errors could be secondary to software glitches, poor algorithm generalization, accidental or intentional misuse or disuse, hardware failure, and others. Therefore, the adherence estimates that we calculate for each patient will be subject to these errors, which may be random or biased to certain study subjects. To mitigate and assess these effects, we will collect survey data from each patient on their use of the smart watches and ask each patient to manually complete a 2-week adherence diary so that we can compare the measured adherence with patient self-report.

A limitation of the final interventional phase of this study is the pilot sample size (N=20) and the absence of a true control group. Although we can compare the interventional cohort with historical controls in the validation cohort, a better comparison would be with a control group with no tracking at all as per the current standard of care. Ultimately, a larger randomized controlled trial (RCT) would be required to adequately assess the effect of an adherence-driven rehabilitation program on recovery. The pilot study we conduct is primarily powered to detect implementation challenges, refine the system design, and estimate the effect size as required preliminaries to funding and carrying out a larger multicenter RCT.

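### Home technique adherence comes from a classifier accepted at just over 80% accuracy, and no stated step allows for its errors, so the reported rate can be biased and differences in it compressed

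*Protocol article*

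**What the plan says.** Under Inertial Data Labeling: "The technique will be labeled as a binary variable", recording whether the treating physiotherapist was satisfied with the performance. The Aim 1 objectives require the system to "classify physiotherapy exercise type and technique with classification accuracy exceeding 90% and 80%, respectively". Construct Validity names the split that decides this: "The by-session cross-validation most closely approximates the use case in the proposed study and will benchmark SPARS performance against our stated measurable objectives". That split estimates performance in "new sessions for subjects with prior training data", and all of it uses labelled clinic sessions.

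The section on home technique adherence then states: "The validated technique classifier will be used to evaluate the technique adherence from the inertial data collected during unsupervised home sessions". On class balance, the same section adds: "It is anticipated that many more correct technique training examples may be available for some exercises".

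In a sentence cut here before its last word, the Discussion (Principal Findings) recognises measurement error: "Therefore, the adherence estimates that we calculate for each patient will be subject to these errors, which may be random or biased to certain study". The mitigation named there is a survey of watch use and a two-week diary. Concurrent Validity adds a comparison of technique calls with physiotherapist logs, by paired *t* test and Bland-Altman plots.

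**The concern.** The share of repetitions that an imperfect classifier calls correct is not the share performed correctly. It mixes true positives with false positives, in proportions that depend on the true rate. The article accepts a classifier on accuracy alone, sets no minimum for sensitivity or specificity, and describes no step between the calls and the home rate.

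The named mitigation does not reach this problem. The section Adherence to Rehabilitation itself says that a written diary cannot show whether exercises were done correctly, and a watch-use survey does not measure technique either. The comparison with physiotherapist logs does address technique, but only in the clinic, and nothing says that its result adjusts the home figure.

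Measuring the rate of home adherence is a headline part of Aim 2. The same measure enters the clinic-versus-home hypothesis, the outcome regressions (Criterion Validity) and the models of adherence on baseline predictors (Univariable and Multivariable Analyses).

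**Working it through.** **Inputs.** From the article: binary label, technique accuracy above 80% (80% taken as the floor), N = 120, target correlation 0.25, power 80%, alpha 5%. Not given, so assumed: Se, Sp and the true correct share p, which is taken over 50% to 95%.

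**The plan's own figure.** The article gives no figure for error in the technique rate. The nearest one is the power for correlations. Two-sided Fisher z: n = ((1.960 + 0.842)/atanh 0.25)² + 3 = 123.3, with power 78.9% at 120. The noncentral *t* for a regression slope gives 80.1% at 120. The stated 80% reproduces.

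**Rate returned.** Measured = p×Se + (1−p)×(1−Sp). With Se = Sp = 0.80:

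| True p | Calculation | Measured | Bias (points) |
|---|---|---|---|
| 95% | 0.76 + 0.01 | 77% | −18 |
| 90% | 0.72 + 0.02 | 74% | −16 |
| 70% | 0.56 + 0.06 | 62% | −8 |
| 60% | 0.48 + 0.08 | 56% | −4 |
| 50% | 0.40 + 0.10 | 50% | 0 |

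If the classifier does better, still with Se = Sp, a true 90% reads 78% at 85% accuracy, 82% at 90% and 86% at 95%.

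**Other pairs with exactly 80% accuracy** (Se + Sp at least 1):

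| Correct share in clinic | Bias at that share (points) | Compression factor Se + Sp − 1 |
|---|---|---|
| 50% | −20 to +20 | 0.60 |
| 70% | −20 to +20 | 0.33 to 0.71 |
| 80% | −20 to +20 | 0 to 0.75 |
| 90% | −20 to −2.5 | 0 to 0.78 |

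The zero at 80% is the classifier that calls everything correct and so already scores 80%. The factor stays below 0.80 at any prevalence. Errors weighted by class must total 0.20 and neither weight reaches 1, so (1−Se) + (1−Sp) exceeds 0.20.

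**Differences.** With Se = Sp = 0.80, patients at 90% and 60% read 74% and 56%: 18 points instead of 30, a factor of 0.60. If both settings are scored by the classifier, a clinic-home difference of 90% versus 70% reads 74% versus 62%: 12 points instead of 20. If clinic rates came from physiotherapist labels and home rates from the classifier, equal true rates of 90% would show a false home deficit of 90 − 74 = 16 points. The article does not say which source the clinic rate uses.

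**Association with outcome.** A common Se and Sp rescales the predictor linearly, so r is essentially unchanged and the outcome-on-adherence slope is multiplied by about 1/0.60 = 1.67. Simulation with N = 120, true r = 0.25, and assumed mean 75%, SD 12 points and 500 calls per patient:

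| Se and Sp across patients | Mean r | Power | Slope relative to truth |
|---|---|---|---|
| Common, 0.80 | 0.24 | 76% | 1.56 |
| SD 5 points | 0.21 | 64% | 1.19 |
| SD 10 points | 0.16 | 43% | 0.72 |

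**The case against.** **This is detail for an analysis plan.** The article defines a percentage for participation only. It gives no formula for technique adherence and does not say that the raw share of calls is the final estimate. An unseen analysis plan could contain a correction. That limits what can be asserted about the sponsor's intention. But the article does fix the instrument, an acceptance bar based on accuracy alone, and the response to measurement error, and that response cannot work for technique by the article's own account. Followed as written, it yields an uncorrected rate.

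**The bias need not be large.** This stands. With 80% correct, Se = 0.875 and Sp = 0.50, accuracy is 0.70 + 0.10 = 80%, and the share called correct is 0.70 + 0.10 = 80%, so the overall rate is unbiased. Patients at other true rates are still misread, because the compression factor is 0.375. The bar is also a floor that may be exceeded.

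**Other checks exist.** The log comparison, label reliability by Fleiss kappa, and equalized odds by sex and compensation status are all planned, and transfer to the home is openly stated as an assumption. These can reveal error, but none is said to adjust the home rate.

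**Correction can do harm.** This also stands. The article expects that exercises may be done wrongly in ways not seen under supervision, so specificity may be lower at home. Suppose clinic Se = Sp = 0.80, home Sp = 0.60 and the true rate is 50%. The raw rate is 0.40 + 0.20 = 60%, and the corrected rate is (0.60 + 0.80 − 1)/0.60 = 67%, which is further from the truth. The unit of the 80% accuracy is also unstated, and Se and Sp for windows of 2 to 4 seconds may not apply to a rate per repetition or exercise.

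**Conclusion.** The point holds in a conditional form. As written, the home technique rate carries the classifier's errors with no stated allowance for them. It can be too high or too low. At the assumed Se = Sp = 0.80 the error is 16 points for a true 90%, 8 points for 70% and none at 50%. At exactly 80% accuracy, differences between patients, settings and predictor groups always shrink by more than 20%, and by 40% at Se = Sp = 0.80. The descriptive rate, the clinic-home contrast and models with adherence as the outcome are affected. Outcome-on-adherence slopes are inflated when Se and Sp are common to all patients.

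A reader might infer two stronger things that the document does not support. One is that any classifier meeting the bar must misstate the overall rate by many points; the size and sign depend on Se, Sp and p, none of which is given. The other is that compression weakens the test of association between technique adherence and outcome. With common Se and Sp, the correlation and P value barely change. Material loss of power needs error rates that differ between patients, and the article gives no figure for that.

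**What to change.** In the data analysis section, report the raw home technique rate and, beside it, (raw + Sp − 1)/(Se + Sp − 1). As a check, (0.74 + 0.80 − 1)/0.60 returns 90%. Specify that:

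- Se and Sp are taken per exercise from the by-session cross-validation already planned, at the same unit (window, repetition or exercise) as the reported rate.
- Intervals come from a bootstrap over patients that re-estimates Se and Sp, so that their uncertainty is carried through.
- Clinic Se and Sp are stated as assumed to hold at home, with a sensitivity range that covers lower home specificity in particular.
- No corrected figure is given where Se + Sp is close to 1.

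The cost is analysis text and computing only, since the labelled data and cross-validation are already planned. The downsides are wider intervals and dependence on the transfer assumption, which is why the raw rate should stay in view. A correction per exercise does not remove variation in error rates between patients.

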### Adherence to Rehabilitation

Adherence is defined as the extent to which the patient follows medical instructions [43]. There is a general assumption that, where a treatment program is efficacious, adherence to the program improves outcome. Patient adherence to a prescribed physiotherapy has been shown to be an important predictor for the successful management of musculoskeletal disorders [9]. However, adherence to standard exercise protocols is often poor with estimates of non or partial nonadherence varying between 50% and 70% [9,11], with worse adherence for home exercise protocols [9].

In the context of physiotherapy and rehabilitation, the concept of adherence is multidimensional [44]. It includes behaviors such as attending clinical appointments, actively participating in physiotherapist-supervised rehabilitation activities, carrying out home exercise and rehabilitation activities, avoiding potentially harmful and contraindicated activities, and wearing protective or therapeutic devices [44]. Physiotherapy clinic attendance is readily measured, and the Sport Injury Rehabilitation Adherence Scale [44] has been used for evaluating in-clinic adherence. The correct use of protective devices has been measured by observations at clinical follow-up [10] and with temperature sensors [45-47].

Measuring adherence to home physiotherapy exercises remains an open problem [48]. Adherence to this component of a rehabilitation program is particularly vital as this activity calls for the greatest level of independent patient engagement in the rehabilitation process. Adherence diaries, in which patients log their independent exercises, is the recommended and most widely used measure of adherence to home exercise [48]. However, adherence diaries have significant limitations. The validity and reliability of the adherence diary have not been established, and poor patient acceptability results in low rates of diary completion [48]. Furthermore, the written diary has no means to establish if the prescribed exercises have been performed correctly. The proposed study will validate a novel method for measuring participation and technique adherence to home shoulder physiotherapy exercises.

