##### Hypotheses

The related hypotheses are as follows:

Exercise technique adherence is better for supervised sessions than at home (*P*<.05).There will be a statistically significant association (*P*<.05) between home physiotherapy exercise participation and technique adherence and the identified clinical outcomes.

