#### Smart Physiotherapy Activity Recognition System-Home Physiotherapy Participation Adherence

The ML algorithms underlying SPARS will be trained in a supervised learning framework to classify (recognize) different activities from the characteristic time series of inertial signals they produce in the smart watch inertial sensors. A detailed description of our implementation and its evaluation are presented in our previous pilot study [15] and our open-source software package for ML time series (seglearn) [116]. Briefly, sensor data are segmented into fixed-length windows (2-4 sec in length) that are learned by a deep convolutional recurrent neural network (CRNN) classifier. Once trained, the classifier can be used to reconstruct a record of activities from the recorded inertial sensor data.

The ML algorithms underlying SPARS will be trained and validated using the labeled inertial sensor data collected during supervised physiotherapy sessions. The trained SPARS algorithms will then generate a record of exercises performed from inertial sensor data collected during unsupervised home sessions and supervised sessions during which synchronous data labeling was not performed. Comparing the quantity and frequency of home exercises measured by SPARS with the prescribed exercises will serve as our measure of participation adherence. Participation adherence will be measured as a percentage of the prescribed activity over each 2-week interval of treatment.

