### Data Analysis

#### Sample Size

The proposed sample size of 120 for clinical validation yields a power of 80% to detect weak correlations (*R*>0.25) between physiotherapy adherence and clinical outcomes, accepting a 5% alpha error. Sample size feasibility was confirmed by the WCP, anticipating a recruitment rate of 70%. The pilot study sample size (20) was used to detect implementation challenges with an incidence rate greater than 15% at a 95% confidence level [124] (not statistically significant differences in clinical or economic outcomes).

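### Home technique has a value only where home exercise was recorded, yet the plan compares it with clinic technique by 2-sample t test and relates it to recovery without participation

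*Protocol article*

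**What the plan says.** All references are to the protocol article.

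- **Participation** has a denominator and an interval: "Participation adherence will be measured as a percentage of the prescribed activity over each 2-week interval of treatment" (section on home participation adherence).
- **Technique** has neither: "The validated technique classifier will be used to evaluate the technique adherence from the inertial data collected during unsupervised home sessions" (section on home technique adherence). Under Inertial Data Labeling, the training label is binary: the treating physiotherapist was or was not satisfied with an exercise that was carried out.
- **Hypotheses under Aim 2.** The first is that "Exercise technique adherence is better for supervised sessions than at home". The second expects an association "between home physiotherapy exercise participation and technique adherence and the identified clinical outcomes".
- **Test for the first.** Under Univariable and Multivariable Analyses, environment (home or clinic) is one of the predictors of adherence, and binary predictors are tested by 2-sample t test.
- **Test for the second.** Under Criterion Validity, change in outcome is regressed on the adherence measures univariately. Management and population subgroup are moderators; participation is not named as a covariate for technique.
- **Sample size.** "The proposed sample size of 120 for clinical validation yields a power of 80% to detect weak correlations" (R above 0.25), "accepting a 5% alpha error".
- **Background.** The Adherence to Rehabilitation section cites "estimates of non or partial nonadherence varying between 50% and 70" percent, and worse adherence for home exercise. The limitations in the Discussion foresee misuse or disuse of the watch, with errors that may fall on particular subjects.

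**The concern.** A technique score needs exercise to score. A patient who does no home exercise, or exercises without the watch, gets 0% for participation and nothing for technique. Three consequences follow.

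1. **Home versus clinic.** Clinic technique can be observed in everyone who attends, home technique only in those with recordings. A 2-sample comparison can therefore contrast two different groups of patients. It also treats two measurements on the same patient as independent.
2. **Technique and recovery.** Engaged patients may both exercise more and exercise better. A univariate slope for technique then carries part of any participation effect, and the result cannot be read as a technique effect.
3. **Power.** The statement for 120 patients covers correlations between adherence and outcomes in general. Technique will have fewer patients than that whenever someone has no recordings.

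At stake are the size of the clinic-home gap in technique and the meaning of the technique-recovery result, both stated hypotheses of Aim 2.

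**Working it through.** **1. The plan's own figure.** Inputs from Sample Size: n = 120, r = 0.25, alpha 5%, taken as two-sided because the side is not stated. With the noncentral t distribution, ncp = r/√(1−r²) × √n, power is 80.1%, and 120 is the smallest n reaching 80%. The stated figure reproduces. The simpler Fisher z formula, used below, gives

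power = Φ(atanh(r)·√(n−3) − 1.96) = Φ(0.2554 × 10.817 − 1.96) = Φ(0.803) = 78.9%.

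**2. Power for technique when some patients are unscored.** The unscored share is an assumption; the documents give none.

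| Unscored | n | atanh(0.25)·√(n−3) | Power at r = 0.25 | r detectable with 80% power |
|---|---|---|---|---|
| 0% | 120 | 2.763 | 78.9% | 0.253 |
| 10% | 108 | 2.617 | 74.4% | 0.267 |
| 20% | 96 | 2.463 | 69.3% | 0.283 |
| 30% | 84 | 2.299 | 63.3% | 0.302 |

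This loss needs no relation between technique and participation.

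**3. Bias in mean home technique.** Assumptions: technique has mean 70% and SD 15 points, participation and technique are jointly normal with correlation ρ, and the lowest fraction f of participators is unscored. The mean among the scored exceeds the cohort mean by

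ρ × SD × φ(z_f)/(1−f), where z_f is the normal quantile at f.

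| f | φ(z_f)/(1−f) | ρ = 0 | ρ = 0.3 | ρ = 0.5 |
|---|---|---|---|---|
| 10% | 0.1755/0.9 = 0.195 | 0 | 0.9 | 1.5 |
| 20% | 0.2800/0.8 = 0.350 | 0 | 1.6 | 2.6 |
| 30% | 0.3477/0.7 = 0.497 | 0 | 2.2 | 3.7 |

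A separate simulation with a true mean of 76.4% and a bounded technique scale gave observed means of 77.4% to 78.9% (ρ = 0.3) and 78.2% to 80.6% (ρ = 0.5). That is 1.0 to 4.2 points too high, the same order.

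**4. The 2-sample test.** With equal SD σ in both settings, n patients measured in both and within-patient correlation c, the 2-sample standard error is σ√(2/n) and the paired one is σ√(2(1−c)/n). The ratio is √(1−c), below 1 for any positive c. With one value per patient per setting, the planned test is therefore less precise than a paired one. The upward bias in step 3 also narrows the clinic-home gap. Both work against the first hypothesis.

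**5. Mixing of technique with participation.** Suppose participation correlates with recovery at 0.25 and technique has no effect of its own. With nobody excluded, the univariate technique correlation is ρ × 0.25, which is 0.075 at ρ = 0.3 and 0.125 at ρ = 0.5. By Fisher z at n = 120, such correlations reach P<.05 in about 13% and 27% of studies, against a nominal 5%.

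**The case against.** **The article fixes no denominator for technique.** If it meant correct exercises as a share of prescribed exercises, a non-participant would score 0 and nobody would be lost. A condensed article may leave that derivation, and rules for empty intervals, to a fuller document. This stands in part: the point depends on the plain reading, a share of exercises performed. The 2-sample test and the univariate regression, however, are stated in the article.

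**A reader might infer that technique will describe only the better participators, and that unscored patients will be common.** The documents do not support either. Anyone with some recorded home exercise over up to 5 months can be scored, poor participators included. The cited 50% to 70% includes partial nonadherence and gives no share with no home exercise. Patients were selected for capacity to do home exercise, and watch use is checked when data are retrieved at clinic visits.

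**A reader might also infer a collapse in power for technique.** If recovery is assumed to follow the product of participation and technique at r = 0.30, with 20% unscored and ρ = 0.3, technique alone has about 31% power against 92% for the product. That contrast mostly restates the assumption. In the same model with nobody unscored, the technique correlation is already only about 0.18 to 0.20, with power of 50% to 59%.

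**Replacing technique by correct exercises as a share of prescribed would do harm.** If technique itself drives recovery at r = 0.25, with 20% unscored and ρ = 0.3, that combined score has about 31% to 33% power against 67% to 68% for technique among the scored. It is dominated by participation. This objection stands and shapes the fix.

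**The Discussion already admits error from disuse and adds a survey and a diary.** These can help show who exercised unrecorded. They cannot supply technique, and the article itself says a diary cannot show whether exercises were done correctly.

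**Conclusion.** The point holds in limited form. Home technique is conditional on recorded exercise, and the two stated analyses do not allow for that.

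- **Home versus clinic:** a 2-sample test on data from the same patients, with mean home technique about 0.9 to 3.7 points too high for the cohort. This assumes 10% to 30% unscored, ρ of 0.3 to 0.5 and SD 15 points. The bias is zero if technique and participation are unrelated, and the documents give no such correlation.
- **Recovery:** a univariate technique slope that cannot be separated from participation.
- **Power:** the 80% for 120 patients does not carry over in full. At r = 0.25 it is about 74%, 69% or 63% with 10%, 20% or 30% unscored.

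Loss of patients alone hardly moves the technique-recovery correlation. In the simulation where technique drives recovery at 0.25, it stayed between 0.235 and 0.247 with 10% to 30% unscored and ρ of 0.3 to 0.5.

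**What to change.** 1. **First hypothesis.** Replace the 2-sample comparison with a within-patient one (paired, or a mixed model over 2-week intervals), restricted to patients and intervals with both home and clinic technique. Report how many patients and intervals are unscored, and the clinic technique of those patients, so that the selection can be seen.
2. **Second hypothesis.** Keep technique among recorded exercises as the technique exposure, label it as conditional on recorded exercise, and enter it together with participation.
3. **Optional secondary measure.** Correct exercises as a share of prescribed may be added as delivered dose, not as the technique exposure. A 0 on it may mean the watch was not worn.
4. **Sample size text.** State that the 80% does not apply in full to technique, and show power over a range of unscored shares.

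**Cost.** Wording and derived variables from data already planned. The technique analyses have slightly fewer patients, and the restricted comparison describes patients with recordings, not the whole cohort. Joint entry with participation also costs precision: the variance of the technique slope grows by 1/(1−ρ²), a factor of 1.10 at ρ = 0.3 and 1.33 at ρ = 0.5. The power to be quoted for technique will therefore be below 80%.

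### The pooled 90% exercise-type target can be met while incorrectly performed exercise is under-recognised, so poor technique may be partly read as non-participation

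*Protocol article*

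**What the plan says.** The Participation Adherence section of the Methods defines the exposure: "Comparing the quantity and frequency of home exercises measured by SPARS with the prescribed exercises will serve as our measure of participation adherence". It fixes the scale: "Participation adherence will be measured as a percentage of the prescribed activity over each 2-week interval of treatment". The same section says that the algorithms "will be trained and validated using the labeled inertial sensor data collected during supervised physiotherapy sessions".

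The Aim 1 objectives set the acceptance thresholds: "classify physiotherapy exercise type and technique with classification accuracy exceeding 90% and 80%, respectively". Construct Validity names the metrics, "cross-validated exercise type and technique classification performance metrics (accuracy, precision, recall, and f1-score) from the labeled inertial data", and chooses the benchmark: "The by-session cross-validation most closely approximates the use case in the proposed study and will benchmark SPARS performance against our stated measurable objectives".

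The Technique Adherence section anticipates two difficulties with technique labels. One is a possible excess of correct examples: "many more correct technique training examples may be available for some exercises". The other concerns errors that clinic sessions do not show: "an exercise may be performed incorrectly in ways not observed during the supervised sessions, leading to class imbalance". It lists possible remedies (resampling, cost-sensitive learning, semisupervised learning, anomaly detection, augmentation), all optional and all for technique evaluation. Nothing comparable is stated for the exercise-type classifier, which learns from the same sessions. Inertial Data Labeling records type and technique together on the same data.

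**The concern.** A home repetition adds to participation only if the type classifier recognises it. If recognition is worse when the exercise is done badly, a patient who does all the prescribed work with poor technique scores below 100%. The shortfall then looks like exercise not done. It also differs between patients: the worse the technique, the larger the loss.

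The stated acceptance criterion would not reveal this. A pooled accuracy is a weighted average over correct and incorrect repetitions. Where correct ones dominate, it says little about the others.

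At stake are the home participation rate, which is a main product of Aim 2, and the second Aim 2 hypothesis, which relates participation and technique to recovery. If technique error leaks into the participation measure, it becomes harder to say which of the two matters. In the pilot, adherence readings will inform treating clinicians, so a patient exercising badly could be taken for one who is not exercising.

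**Working it through.** **The plan's own figure.** The 90% target is a threshold and is not derived from inputs, so there is nothing to reproduce. The question is what it guarantees.

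**Inputs.**
- From the article: the definition of participation, the target of more than 90%, and by-session cross-validation on supervised data.
- Assumed, because the article gives no values: c, the share of labelled clinic repetitions that are correct; r1 and r0, type recall on correct and incorrect repetitions; g, a patient's share correct at home. A repetition given the wrong type is treated as lost, and false detections are ignored.

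**Formulas.**
- Pooled clinic accuracy = c·r1 + (1−c)·r0
- Measured participation of a patient who does everything prescribed = g·r1 + (1−g)·r0

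**Step 1: does the target pass?** Take c = 0.90 and r1 = 0.95.
- r0 = 0.70: 0.855 + 0.070 = 92.5%
- r0 = 0.85: 0.855 + 0.085 = 94.0%

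Both pass.

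**Step 2: what does a full participant read?** The true value is 100%.

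| Correct at home (g) | r0 = 0.70 | r0 = 0.85 |
|---|---|---|
| 60% | 0.57 + 0.28 = 85% | 0.57 + 0.34 = 91% |
| 40% | 0.38 + 0.42 = 80% | 0.38 + 0.51 = 89% |

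The slope on g is r1 − r0. Each 10 points of technique lost costs 2.5 points of measured participation at r0 = 0.70, and 1 point at r0 = 0.85.

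**Step 3: how low can r0 be at a pooled 90%?** Solve r0 = (0.90 − c·r1)/(1−c), with zero as the floor.

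| c | r1 = 0.95 | r1 = 0.99 |
|---|---|---|
| 0.70 | 78% | 69% |
| 0.80 | 70% | 54% |
| 0.90 | 45% | 9% |
| 0.95 | 0% | 0% |

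These are arithmetic limits, not predictions. They show that reaching the target places almost no constraint on r0 when correct repetitions dominate, and a moderate one when they do not.

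**Step 4: technique, conditionally.** If technique were scored only on recognised repetitions, and scored perfectly, the measured share correct at g = 0.60 would be 0.57/0.85 = 67% or 0.57/0.91 = 63%, against a true 60%. The article does not state that rule.

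**Step 5: do the stated checks see it?** The three fold strategies (by-subject, by-session, within-session) vary patient, session and repetition. None is defined by technique. The physiotherapist logs in Concurrent Validity come from supervised sessions. The diary is the one comparison with home data on number and type of exercises. It covers two weeks, is self-reported and carries no technique assessment, and the Introduction (Adherence to Rehabilitation) says that the validity and reliability of such diaries are not established.

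**The case against.** Several points against the concern stand.

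- A reader might infer that badly performed exercise drops out of both adherence measures. The article does not say so. It describes a second algorithm applied to home inertial data, without stating that only recognised segments are scored. The technique effect, and any weakening of the supervised-versus-home hypothesis, is therefore conditional.
- A reader might take it that most clinic repetitions are expected to be correct. The text says only that this may be so for some exercises, and gives no share.
- The anticipated imbalance is written about the technique classifier. Carrying it to the type classifier is an inference. How far poor technique disturbs type recognition from a wrist sensor is unknown.
- A repetition assigned to another prescribed exercise may still be counted, so treating every misclassification as lost gives the larger loss. Classification is on windows of 2–4 seconds, and how windows become counts is not described.
- A reader might set any correlation induced between the two adherence measures against the R of 0.25 in Sample Size. That figure concerns adherence and clinical outcomes, so the comparison is not valid.
- The plan has partial safeguards. Diary and SPARS counts are compared by paired t test and Bland-Altman plots, where exercise done badly but logged as done would appear as undercounting. The Discussion concedes that home generalisation is assumed and that errors may be biased to certain subjects.
- Listing recall among the metrics does not exclude a breakdown by technique, and a condensed article may omit tabulation detail.

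These points limit the size and remove the claim about both measures. They do not rescue the acceptance criterion. The article does fix a pooled target, and that target can pass while recognition of incorrect exercise is poor.

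**Conclusion.** The point holds for participation. The pooled target of more than 90% does not show that incorrectly performed exercise is recognised, and unrecognised exercise lowers participation as if it had not been done. On the assumed recalls of 95% and 70–85%, a full participant with 60% correct at home reads 85–91%. The true size could be larger, smaller or nil, because neither the share correct nor recall by technique is given, and the calculation assumes that misclassified repetitions are lost. For technique, the statement is only conditional: home technique would look too good if scoring were restricted to recognised segments. This is a worthwhile improvement to the acceptance criterion, not evidence that the adherence measures will fail.

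**What to change.** In Construct Validity, report exercise-type recall separately for repetitions labelled correct and incorrect, with intervals, under the by-session and by-subject folds. In the Aim 1 objectives, judge the type target of more than 90% on both groups.

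If recall on incorrect repetitions is lower, extend the imbalance remedies of the Technique Adherence section to the type classifier, and add a sensitivity analysis of participation over a range of recalls. State whether home technique is scored only on segments that the type classifier recognises.

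State also that a split of clinic data cannot test error forms that never occur in clinic, and that for these the diary comparison in Concurrent Validity is the only, imperfect, check.

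The cost is a tabulation and possibly one re-weighted training run; both labels are already recorded together, so no new data are needed. The downside is a wider interval for the smaller incorrect class and a possibly less favourable headline figure.
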